#### Randomization and access to the intervention

Since there is a high probability for cross-contamination within training sessions, randomization will occur by training group (all individuals attending a specific training will be randomized to the same arm). The instruction sheet will give them information for logging on to the Tobacco Tactics website or calling the 1-800-QUIT-NOW telephone quit line. All subjects will be given time to make this first contact with the intervention during the training session where they will have access to a computer or telephone. After participating in the web-based Tobacco Tactics intervention, participants may continue to access the website from home, but this is not necessary as repeated access has not always been shown to increase efficacy of web-based interventions [25]. Both the intervention and control group will receive follow-up telephone calls. Both interventions are described in detail below.

#### Follow-up

Since return rates are lower for online surveys, to assess quit rates, we will use a two-step approach for collecting 30-day and 6-month follow up-surveys [41]. Subjects will initially be asked to complete the online survey. Those subjects who do not complete the online survey will then be mailed a paper survey to increase response rate. All subjects will also be mailed a NicAlert urinary cotinine test strip to confirm tobacco use status at the 6-month follow-up time point only (as the 30-day time point may give a false positive for smoking due to the use of nicotine replacement therapy). Participants in both study arms can receive a total of $50 remuneration (in the form of gift cards) for completion of surveys and cotinine tests.

### Description of Tobacco Tactics web-based intervention

#### General description

The Tobacco Tactics website was developed based on a manual tested in a prior clinical trial and is in keeping with guideline recommendations for treatment of tobacco [42]. The content is written at an 8^th^ grade reading level. To ensure confidentiality participants are instructed to use their study identification (ID) as their user name. Participants create their own password at the time of first log-on. The home page is illustrated with colorful graphics and video of a testimonial from an Operating Engineer who quit smoking. The left side of the home page has “buttons” that link to modules that have been used in our Tobacco Tactics intervention. The top of the homepage has informational tabs. See Figure 2.

**Figure 2 F2:**
[figure not shown]
Sample Screen Shot of Tobacco Tactics Website.

#### Preparing to quit

The left side of the homepage provides information on the perceived benefits and barriers to quitting. The General Information button provides content on the Patterns of Smoking among Operating Engineers, Health Consequences of Tobacco Use, Immediate Physical Effects from Cessation, Chemicals in Cigarettes including a scrolling list of the chemicals, and Second Hand Smoke. The Are You Ready for Change button provides interactive self-assessments on reasons for quitting, nicotine dependence, and identification of smoker type which then provide the Operating Engineers with tailored messages.

#### Medications

Another button on the left side of the homepage links to a review of the medications available to assist with cessation and provides a suggested medication algorithm (enhancing self-efficacy). Operating Engineers will be offered their choice of a full supply of over-the-counter nicotine patch, gum, or lozenge. This is similar to what is done in other internet intervention studies [27], and is also done by the 1-800-QUIT-NOW quit line (control group). Those who have failed nicotine replacement therapy in the past will be encouraged to discuss prescription medications such as bupropion or varenicline with the study nurse who can assist with coordination of medications with their health care provider. See Figure 3 for additional screen shots.

**Figure 3 F3:**
[figure not shown]
Sample Tobacco Tactics Web Pages.

#### Active quitting

Additional buttons on the left side of the homepage include information to enhance self-efficacy. The Goal Setting button has the Operating Engineer prepare for quitting by discarding all cigarettes, cleaning the car, informing family and friends, and setting a quit date. The Handling Thoughts About Tobacco button assists with assessing high risk situations and common triggers for relapse. The Coping With Cravings button gives tips based on their smoker type. The Coping With Relapses button discusses the role of alcohol, depression and relapse. The Common Problems in Quitting button discusses withdrawal symptoms and weight gain. The Life As A Non-Tobacco user button is designed to highlight how positive life can be as a nonsmoker. Additional buttons provide relaxation exercises and resources.

#### Informational tabs

“Tabs” across the top of the homepage include My Page which saves the participants’ data from interactive exercises. The tab About Us includes information about the study team. There is a tab to Contact Us. The Messages tab allows the study nurse to post messages for individual participants. The Latest News tab is a newsfeed from a smoking cessation blog. There is also a tab for an e-community.

#### Interactivity and tailoring

To enhance self-efficacy and perceived benefits and to reduce barriers, the treatments link will provide interactive cognitive behavioral therapy exercises tailored to the individual including a self-assessment of their tobacco habit, calculating a score about their level of addiction, identifying their smoker type, calculating money savings, preparing for quitting, (e.g., cleaning the car of cigarette butts, etc.), change plan work sheet, and coping with relapses. Additional interactive components will provide mechanisms for tobacco users to assess their smoking habit, set a quit date, and monitor weekly progress.

#### Nurse counseling

Since studies have shown that telephone and nurse counseling is efficacious [30-32] and tailored telephone and regular postal mail cessation interventions have been found to be efficacious among construction workers [43], the Tobacco Tactics web-based intervention will be enhanced with follow-up nurse telephone and/or email counseling contacts at 2, 7, 14, 21, and 30 days after the training. The follow-up contacts will reinforce the initial website visit, promote skill building, and monitor pharmacologic treatment. The nurse will not provide personal medical advice, but only expand on the information on the Tobacco Tactics website.

#### E-community/forum

Since peer support has been shown to enhance behavioral interventions [44], there will also be a nurse-monitored e-community to enhance self-efficacy. The nurse will serve as group moderator for the e-community and answer questions and post questions to stimulate group discussion. Each participant will be asked to select a pseudonym in order to establish an on-line identity while maintaining privacy. Following work by Lorig et al. [45], the e-community will be used to provide social support, both peer and professional. The e-community will allow intervention participants to post messages, ask questions and share success stories. While a disadvantage of the electronic forum is that the participant has to log in to both read and post messages, an advantage is that it will prevent e-mail overload and all postings can be monitored to prevent inappropriate messages or communication. The nurse will be trained to indentify messages deemed inappropriate, these messages will be deleted, the person that posted the message will be counseled and, if such behavior continues, they will have their access privileges revoked.

#### Informatics for the project

The Tobacco Tactics website for Operating Engineers was developed by Allen Wayne, LTD, who will also provide backup informatics during the course of the study. The website will be housed on a secure server at the University of Michigan.

### Control intervention

#### Principles of control group design

A recent article provides valuable insights into the design of control group conditions in clinical trials for behavioral interventions [46]. A fundamental principle is that the experimental and control conditions should be as equivalent on as many elements as possible including time spent, parallel recruitment periods and follow-up times, and attention given to participants. Both the intervention and control conditions should be of interest and value to the participants; control groups should not burden participants with worthless tasks as this may result in drop out of control group participants. Ethical considerations about withholding standard treatments should also be considered. When these conditions are met, the internal validity of the intervention is achieved.

#### Rationale for comparison arm

Given the principles of control group design, several options were considered as comparison arms for this study. One option was a “placebo” website (e.g., physical activity website); however, the literature shows that cessation websites work and we feel ethically obligated to provide some sort of cessation treatment. Another option was referral to another cessation website such as smokefree.gov, this being one of the better sites currently available; however, smokefree.gov is largely informational and has no interactive exercises or tailored messages and studies have shown that websites of this nature, while informational, are highly unlikely to engage participants and effect behavior change. A third option was to refer to an existing cessation treatment website; however, these sites often cost money and may not be well designed or marketed to appeal to Operating Engineers. After careful deliberation, we chose to compare the website to the 1-800-QUIT-NOW telephone quit line currently available in Michigan. The comparison arm was designed to answer the question that we felt would be of most value: Can the Tobacco Tactics website for Operating Engineers produce results better than an efficacious cessation treatment that is currently available in the community?

#### Description of 1-800-QUIT-NOW telephone quit line

The 1-800-QUIT-NOW quit line is a national program, run by each individual state, so the program can vary from state to state, however, we are only recruiting in Michigan so all participants will receive the same intervention. The first time someone calls the quit line, they will receive a personal coach who will assist them in setting a quit date and making an individualized quit plan. The personal coach also will provide on-going support with up to five telephone coaching sessions around the caller’s quit date. The first session usually lasts between 20–30 minutes and includes the intake evaluation and setting up appointments for the remaining counseling sessions. The length of the typical follow-up session is usually 20–40 minutes. Similar to our Tobacco Tactics intervention, the Michigan quit line provides free nicotine replacement therapy (patches or gum) for residents who are either uninsured or for those who have insurance that will not cover nicotine replacement therapy.

#### Equivalency across comparison groups

In keeping with the aforementioned principles of designing control groups, the Tobacco Tactics website and the 1-800-QUIT-NOW control conditions have been designed to be as equivalent as possible, in terms of time spent, parallel recruitment and follow-up, attention given to participants, and access to nicotine replacement therapy. Both groups are provided with a cessation intervention, nicotine replacement therapy, and equal numbers of follow-up contacts.

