**Methods/Design:**

This will be a randomized controlled trial (N = 184). Both interventions will be offered during regularly scheduled safety training at Local 324 Training Center of the International Union of Operating Engineers and both will include optional provision of over-the-counter nicotine replacement therapy and the same number of telephone contacts. However, the Tobacco Tactics website has graphics tailored to Operating Engineers, tailored cessation feedback from the website, and follow up nurse counseling offered by multimedia options including phone and/or email, and/or e-community. Primary Analysis of Aim 1 will be conducted by using logistic regression to compare smoking habits (e.g., quit rates) of those in the intervention arm to those in the control arm. Primary analyses for Aim 2 will compare process measures (e.g., medications used) between the two groups by linear, logistic, and Poisson regression.

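### The protocol says both arms get nicotine replacement and equal follow-up contacts, but its own arm descriptions do not support this, so a difference cannot be credited to the website component alone

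*Protocol article*

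**What the plan says.** Three places in the protocol article present the arms as alike.

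- The abstract (Methods/Design) says of the two interventions that "both will include optional provision of over-the-counter nicotine replacement therapy and the same number of telephone contacts".
- Equivalency across comparison groups says they were "designed to be as equivalent as possible, in terms of time spent, parallel recruitment and follow-up, attention given to participants, and access to nicotine replacement". The sentence after it drops that qualification: "Both groups are provided with a cessation intervention, nicotine replacement therapy, and equal numbers of follow-up contacts".
- Medications, after describing the NRT offer in the Tobacco Tactics arm, adds that the quit line does this too.

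The descriptions of what each arm receives read as follows.

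- Tobacco Tactics, NRT (Medications): "Operating Engineers will be offered their choice of a full supply of over-the-counter nicotine patch, gum, or lozenge". No insurance condition is stated.
- Quit line, NRT (Description of 1-800-QUIT-NOW telephone quit line): "the Michigan quit line provides free nicotine replacement therapy (patches or gum) for residents who are either uninsured or for those who have insurance" that does not cover it.
- Tobacco Tactics, contacts (Nurse counseling): "follow-up nurse telephone and/or email counseling contacts at 2, 7, 14, 21, and 30 days after the training".
- Quit line, contacts (same Description section): a ceiling of five telephone sessions around the quit date. The first includes intake and "setting up appointments for the remaining counseling sessions".

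Principles of control group design lists elements on which arms should match as far as possible and concludes: "When these conditions are met, the internal validity of the intervention is achieved".

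**The concern.** A reader who is told that NRT and contacts were the same in both arms will attribute any difference in quit rates to what is left, chiefly the tailored website. The Discussion points that way: it describes a rigorous comparison of the website with the quit line and looks ahead to wide dissemination of a web-based intervention.

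NRT is not a neutral background item here. The Cessation interventions section reports that NRT increases quit rates at worksites, and that counselling combined with medication is efficacious. If one arm had easier access to NRT, part of a difference could come from supply, and a later rollout of the website without study-supplied NRT might not reproduce the result.

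**Working it through.** The point is mainly a comparison of text. The planned sample size of 92 per group is not in dispute and does not change.

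**Step 1. Set the arm descriptions side by side.**

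| Element | Tobacco Tactics arm | Quit-line arm | Stated as alike in |
|---|---|---|---|
| Who gets free NRT | All offered; no insurance condition stated | Uninsured residents, or insurance does not cover NRT | Abstract; Medications; Equivalency |
| Products | Patch, gum, lozenge | Patch, gum | Same |
| Amount | Full supply | Not stated | Same |
| Follow-up contacts | 5, on fixed days | At most 5, around the quit date | Abstract; Equivalency |
| Mode | Telephone and/or email, plus a nurse-monitored e-community | Telephone | Abstract (telephone contacts) |

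**Step 2. NRT.** Take a participant whose insurance covers NRT. In the Tobacco Tactics arm the study offers that person a full supply. In the control arm, as described, the quit line does not provide it free. Both descriptions cannot hold together with the statements that the arms are alike on NRT.

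**Step 3. Contacts.** The nurse schedule (days 2, 7, 14, 21 and 30) has 5 follow-up contacts. The quit line allows two readings:

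- intake is one of the five: at most 5 − 1 = 4 follow-up sessions;
- intake is separate: at most 5 follow-up sessions.

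The counts match only on the second reading, and only for callers who use every session. Because nurse contacts may be emails, the number made by telephone is not fixed either, so the abstract's statement about telephone contacts is not secured.

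**Step 4. Can the NRT contribution be sized?** Not from the documents. They give no NRT uptake by arm, no insurance coverage rate and no quit rate without NRT. An illustration needs three inputs:

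- *p*, the quit rate with NRT. The range 15–35% is the one reported in Cessation interventions for counselling plus medication. Using it for the Tobacco Tactics arm, with every member taking NRT, is an assumption.
- *R*, the ratio of quit rates with and without NRT: assumed 1.2 to 2.0.
- *f*, the share of controls who go without NRT: assumed 25% to 100%.

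Gap from NRT alone = *p* × *f* × (1 − 1/*R*).

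- Low: 0.15 × 0.25 × (1 − 1/1.2) = 0.006, or 0.6 points.
- Middle: 0.25 × 0.50 × (1 − 1/1.5) = 0.042, or 4.2 points.
- High: 0.35 × 1.00 × (1 − 1/2.0) = 0.175, or 17.5 points.

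The high case is an outer bound. It has every control going without NRT, although the quit line supplies some of them and others have insurance that covers it. Set against the 16-point difference in the Power analysis section, the range runs from negligible to the whole target. It therefore shows only that the size depends on inputs the documents do not supply.

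**The case against.** The strongest reply is that the trial asks a pragmatic question. Rationale for comparison arm asks whether Tobacco Tactics can do better than an efficacious treatment already available in the community, and the quit line's own NRT rules belong to that treatment. The abstract lists nurse counselling and the e-community openly as features of the experimental arm, and Data analysis credits a difference to the Tobacco Tactics intervention. This stands. A reader might infer that unequal components bias the trial, or that no difference can be credited to Tobacco Tactics. The documents do not support that: unequal ingredients do not bias a randomised comparison of one package with another.

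Four further replies have force.

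- **Contacts.** Both arms carry a nominal five, and both make a first contact during the training session (Randomization and access to the intervention). A reader might infer that controls get at most four follow-up sessions, but that is only one reading. The imbalance could also favour the control arm: quit-line follow-up sessions typically last 20–40 minutes, while no length is given for nurse contacts.
- **Internal validity.** The control-group principles come from a cited article and name time, recruitment and follow-up periods, and attention. They do not name NRT, so it is too strong to say that the protocol stakes its validity on equal NRT.
- **Number of contacts as an active ingredient.** The Background supports medication, nurse advice and telephone counselling. It says nothing on how many contacts matter.
- **Access through insurance.** Controls outside the free offer are those whose insurance covers NRT, so they have another route to it. The real gap may be small.

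The softer phrase about being as equivalent as possible does not rescue the text, because the sentence after it is unqualified. None of these replies removes the conflict on NRT.

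**Conclusion.** The point holds in a limited form. The equivalence statement is contradicted by the protocol's own account of NRT and is unsupported on the number of contacts. The comparison of the whole Tobacco Tactics package with the quit line as available remains valid. A difference cannot be assigned to the website component alone on the ground that NRT and contacts were equal.

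No size can be given. A reader might infer from an illustration such as the one above that a set number of the 16 points is due to NRT, but the uptake and effect inputs are assumed. The conclusion rests on the article's wording. If the arms were in practice treated alike, it is the arm descriptions that need correcting. No sample size, randomisation or test is affected.

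**What to change.** 1. Reconcile the abstract, Medications, Nurse counseling, the quit-line description and Equivalency across comparison groups on who gets NRT, which products and how much, and on how contacts are counted and by what mode. Which NRT or contact rule is right is for the investigators to state; this review takes no view.
2. Withdraw the equivalence wording unless it is made true. The article reports 135 of the planned 184 already randomised, so the statement must also describe what those participants received.
3. State the comparison and any conclusion as the whole package (website, nurse contacts, e-community and study-supplied NRT) against the quit line as available.
4. Report NRT receipt and contacts by arm next to the primary 6-month result. Medications used and contacts with the intervention are already collected in both arms under Process evaluation (Aim 2).

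The cost is wording and the placing of a table. The downside is a narrower conclusion: the trial will not show that the website itself is responsible for any benefit.

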### Measures

#### Outcome evaluation (Aim 1)

To measure 30-day and 6-month cessation, we will ask participants in both groups if they have smoked cigarettes, even a puff, within the last 7 days [47]. Tobacco use status at 6 months will be confirmed by biochemical verification in the form of urinary cotinine test strips sent by mail. Harm reduction will also be assessed including cigarettes smoked/day, number of quit attempts, and nicotine addiction. Nicotine dependence will be assessed using the Fagerstrom Test for Nicotine Dependence (FTND) [48]. The Health Belief Model will be tested by questions (rated on a 5-point scale) used in our prior studies including: 1) Perceived Benefits: How important do you think quitting smoking is to your health? 2) Perceived Barriers: How difficult do you think it would be to quit smoking? and 3) Self-Efficacy: How confident are you that you will be able to stay off cigarettes? Based on current literature and pilot work done in this population, alcohol use [49], depression [50], stress [51], social support [52], comorbidities [53], and demographics [54,55] all may influence quit rates and therefore will be measured by valid and reliable instruments and controlled for as necessary in the analysis. Demographics have been shown to influence quit rates [54,55], so questions will be asked about age, gender, race, marital status, educational level, and veteran status.

#### Process evaluation (Aim 2)

For the tobacco users that are randomized to use the website, process evaluation will determine the: a) number of times they signed onto the website; b) medications used; c) number of nurse email/telephone calls per patient; d) helpfulness of the nurse/coach; and e) willingness to recommend the intervention to others (5 point scale ranging from strongly disagree to strongly agree) and satisfaction with the website. Similar survey questions will be asked of those randomized to the 1-800-QUIT-NOW telephone quit line intervention including: a) contacts with intervention; b) medications used; and c) willingness to recommend the intervention to others.

